## Background

Depression affects 26% - 44% of older adults using home care services - at least twice that among older persons in general [1-3]. They also suffer from a fourfold increase in more severe forms of depression than the general population [4]. Yet, this population is one of the most undertreated populations for mental health [1,4-6]. In one study only 22% of depressed older home care clients were found to be in receipt of any antidepressant treatment, and only 15% received adequate treatment [1]. Untreated or undertreated depression in older adults is a significant public health concern, associated with greater morbidity and dependency, functional decline, diminished quality of life, poor adherence to medical treatment, increased demands on family caregivers, increased use of healthcare services and death [2,3,5,7-9]. The costs of health care associated with depression are staggering. Annual costs for depression in Canada are estimated at over 14.4 billion [10], attributable to primary care visits, hospitalization, and medication [11]. These costs are compounded by indirect costs, such as costs to family caregivers, many of whom have depression themselves.

Older home care clients using personal support services (PSS) are at particularly high risk for depression, compared to other home care clients. This segment of the population, who represent approximately 75-80% of home care users [12], are typically over 70 years of age and have co-existing chronic and acute health conditions [13], functional disabilities, cognitive impairment, or social support networks that are overextended or prone to breakdown with any shift in their health and well-being [14-16]. These are the same conditions that are associated with an increased risk of depression [2,17,18]. The magnitude of the problem has the potential to increase relative to the increasing numbers of those over 65 years of age [19], the associated increase in the prevalence of depression [17] and the increasing demand for PSS [20]. Home care is the largest component of community-based services and one of the fastest growing components of the health care system [21]. In Canada, approximately 90% of the expenditure for home care services for older adults with ongoing care needs is for PSS and 10% is for professional services [22].

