### Sample Size Calculation and Feasibility of Recruitment

The sample size was calculated to detect a clinically important difference of 3.5 points in mean change from baseline to 6 months in the primary outcome measure, severity of depressive symptoms, using the Centre for Epidemiological Studies in Depression (CES-D) Scale [87]. In the general population, a difference of this size would be associated with increased risk of functional decline, stroke, myocardial infarction and mortality [88,89]. Using a standard deviation of 9.0 as a conservative estimate and a difference of -3.5 points, a base sample size of 105 was estimated to be sufficient to address this primary outcome (two-tailed alpha = 0.05; beta = 0.20).

Our primary analysis of the factors that predict the severity of depressive symptoms will be addressed using regression analysis with the change (6-month-baseline) in the CES-D score as the dependent variable. The predictor variable: dose of the intervention (low, moderate, high), and potential confounding variables representing known risk factors for depression (female gender; prior history of depression; antidepressant medication use; living alone; cognitive impairment; family caregiver with depression; widowed, divorced or separated; low income (< $40,000 per annum); co-morbid health conditions; hospital admission in last 6 months; age; use of three or more prescription medications; presence of anxiety disorder; low social support; poor health-related quality of life; excessive consumption of alcohol; taking depressogenic medications; recent stressful life event; presence of risk factors for cardiovascular disease; and chronic pain) [17], will be included in the initial models. Norman & Streiner [90] recommend 5 participants for each independent variable included in a regression model; therefore, since the study included twenty independent confounding variables, and taking into account a possible 20% attrition rate, the minimum sample size was calculated as follows: 105 + (5 × 20) = 205 plus 20% = 246. In order to ensure a case to variable ratio that would suffice the number of variables, an even larger sample of 250 participants was planned for recruitment. The estimated attrition rate was based on an earlier trial in which 84% of the study participants completed the 6-month follow-up [70].

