#### Data Analyses

Quantitative data will be cleaned, checked for out of range values, skip pattern problems and duplicates. Tests of normality will be completed to determine appropriateness of statistical methods. All analyses will be performed using the Statistical Package for the Social Sciences (SPSS) version 19.0 for Windows on an intention-to-treat basis. All statistical tests will be performed using two-sided tests at the 0.05 level of significance. For all models, the results will be expressed as effect (or odds ratio for binary outcomes), standard errors, corresponding two-sided 95% confidence intervals (CI), and associated p-values. Descriptive analysis of demographic characteristics will be expressed as a mean (standard deviation [SD]) or median (minimum-maximum) for continuous variables and count (percent) for categorical variables.

The primary analysis to address the main outcome measure (change in mean scores from baseline to 6-months in the severity of depressive symptoms) will be tested using analysis of covariance (with pre-intervention scores as covariates). The factors that predict the severity of depressive symptoms will be addressed using regression analysis with the change (6-month-baseline) in the CES-D score as the dependent variable. The predictor variable dose of the intervention (low, moderate, high), and potential confounding variables representing known risk factors for depression, will be included in the initial models. Model assumptions and goodness-of-fit will be assessed by examining the residuals for model assumptions and chi-squared test of goodness-of-fit or qqplots and Hosmer-Lemeshov tests for logistic regression models. We will assess multicollinearity by investigating associations among the confounding variables. For linear models, we will use the variate inflation factor (VIF) to assess collinearity. Variables having a VIF greater than 10 will be considered collinear and will be excluded from the analysis [110]. The secondary hypothesis of change in the prevalence of depressive symptoms, anxiety, HRQOL, cognitive impairment, and the rate of depression treatment from baseline to 6 and 12 months, will be tested using multiple regression (or logistic regression for binary outcomes) using the same approach as in the primary analysis. The possibility of co-interventions occurring such as mental health-related counselling and support programs will also be monitored.

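### The logistic models for the binary secondary outcomes may inherit a 21-to-23-term list whose sample-size allowance was made for a linear model only; the plan should say which approach carries over and cap or penalise it

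*Protocol article*

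**What the plan says.** Under Sample Size Calculation and Feasibility of Recruitment, the article describes a regression with 6-month change in CES-D as the dependent variable. Its predictors are intervention dose in three levels and 20 listed risk factors as potential confounders. For this model the article cites a textbook that is said to "recommend 5 participants for each independent variable included in a regression model". It adds 5 × 20 to a base of 105 and inflates for attrition. The target is then raised to 250: "In order to ensure a case to variable ratio that would suffice the number of variables".

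Under Outcome Evaluation, Data Analyses, the primary outcome is to be tested by analysis of covariance with the pre-intervention score as covariate. The next sentences describe the regression on dose and confounders, which enter what the article calls the initial models. The secondary outcomes, at 6 and 12 months, "will be tested using multiple regression (or logistic regression for binary outcomes) using the same approach as in the primary analysis". Results for binary outcomes are to be given as odds ratios with 95% confidence intervals and p-values. The binary outcomes include CES-D at or above 21, anxiety above a GAD-7 cut-off, cognitive impairment by SMMSE cut-off, and depression treatment.

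**The concern.** In a linear model the information available to estimate coefficients grows with the number of participants. In a logistic model it is limited by the smaller of the two outcome categories. A participants-per-variable allowance made for a continuous outcome therefore does not carry over to a binary one.

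If the full list of dose and confounders goes into each logistic model, the number of events (or non-events) per estimated term may be small. Ordinary maximum likelihood then pushes odds ratios away from 1, and interval coverage can fall below nominal. Dose and risk-factor effects would look stronger than they are. The Discussion intends to use findings on participant characteristics to target scarce resources, so inflated associations would have a practical consequence.

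**Working it through.** **Reproducing the plan's figure.** The inputs, all from the sample-size section, are "a clinically important difference of 3.5 points in mean change from baseline to 6 months", "Using a standard deviation of 9.0 as a conservative estimate and a difference of -3.5 points" and "two-tailed alpha = 0.05; beta = 0.20". The stated result is that "a base sample size of 105 was estimated to be sufficient to address this primary outcome".
- 105 is reproduced by the exact two-sample t calculation, as a per-group number (the normal approximation gives 104).
- 105 + 5 × 20 = 205, and 205 × 1.2 = 246, rounded up to 250. This reproduces the stated total.
- The base of 105 does not match a one-sample calculation (54 by t). That is a separate matter and does not bear on this point.

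**Number of terms, on the multi-predictor reading.** The listed confounders count to 20. Dose adds 1 term if ordinal or 2 if coded as contrasts, giving 21 or 22. A separate baseline value of the outcome gives up to 23.

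**Number analysed.** 250 × 0.80 = 200 with the planned 20% attrition. 250 × 0.84 = 210 with the 84% six-month completion of the earlier trial that the article cites. Completers are the natural base because multiple imputation is listed only as a sensitivity analysis.

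**The linear model.** With 22 terms, 200/22 = 9.1 and 210/22 = 9.5 participants per term. The CES-D regression exceeds the plan's ratio comfortably.

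**The logistic models.** Events per term = N × min(p, 1 − p) / terms.

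| Prevalence | 200, 23 terms | 200, 22 terms | 210, 22 terms | 210, 21 terms |
|---|---|---|---|---|
| 50% | 100/23 = 4.35 | 100/22 = 4.55 | 105/22 = 4.77 | 105/21 = 5.00 |
| 22% | 44/23 = 1.91 | 44/22 = 2.00 | 46.2/22 = 2.10 | 46.2/21 = 2.20 |
| 15% | 30/23 = 1.30 | 30/22 = 1.36 | 31.5/22 = 1.43 | 31.5/21 = 1.50 |

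The 22% comes from the Background ("In one study only 22% of depressed older home care clients were found to be in receipt of any antidepressant treatment"); the 15% is the adequate-treatment rate in the same sentence. Both are illustrations, because the article gives no expected rates for its own sample.

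If all 250 contribute, a 50% outcome gives 125/23 = 5.4 to 125/21 = 6.0.

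For 5 events per term with 22 terms, N = 5 × 22 / p: 220 completers at 50%, 500 at 22% and 734 at 15%.

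**What this does to the estimates.** Two simulations used 200 completers, 22 terms and a true odds ratio of 2, fitted by maximum likelihood. Covariate prevalences and effects were assumed.

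| Prevalence | Inflation of log OR, run A | Inflation of log OR, run B | 95% CI coverage, run A |
|---|---|---|---|
| 50% | 9.8% | about 13% | 94.5% |
| 22% | 24.0% | about 17% | 93.7% |
| 15% | 25.8% | about 22% | 93.1% |

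Run B gave coverage of 92 to 94% and 6 to 7% false positives per null term. In run A, 2.7% of fits failed at 15% prevalence. In run B a Firth-penalised fit of the same model removed the bias and brought coverage to about 95 to 96%.

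**The case against.** The strongest reply is that the premise is only one reading. The Data Analyses section attaches the word primary to the ANCOVA with baseline score. If that is what carries over, each logistic model holds a baseline value and perhaps dose, and the problem disappears. This stands as a real ambiguity. The multi-predictor reading is nevertheless the more natural one: the sentence names multiple regression, and the sample-size section calls the regression on dose and confounders the primary analysis of predictive factors.

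Other parts of the reply also stand:
- A reader might infer that the whole study was sized at 5 participants per variable. It was not; the allowance was added to a base of 105. The article also makes it only for the CES-D regression and promises no ratio for binary outcomes.
- A reader might infer that every binary outcome must fall below 5 events per term. At 50% prevalence this depends on analysing completers and on the term count: 210 completers with 21 terms reach 5.0, and all 250 exceed 5. The baseline value may also be largely counted already, since antidepressant use, cognitive impairment and anxiety disorder are among the 20 confounders. The article sets no events-per-term threshold.
- A reader might take the 134 participants entered to date as the final sample and compute far worse figures. Recruitment was still under way, and the plan is for 250.
- The trial's own treatment rate could differ from 22%. Clients already on treatment are eligible, and the intervention supports antidepressant management.

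It can also be said that calling the models initial foresees reduction, and that a condensed article leaves such detail to the full plan. That does not settle the point. The only removal rule stated is a VIF above 10 for linear models, and the sentence on binary outcomes can be read as fixing an approach that suits them poorly.

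**Conclusion.** The point holds conditionally. If the multi-predictor model is carried to the binary outcomes, the information per term is about 4.3 to 5.0 at best among 200 to 210 completers, and about 2 or 1.4 at rates of 22% or 15%. Odds ratios are then likely to be inflated, by roughly 10 to 25% on the log scale, with coverage of about 92 to 94%. Inflation is greatest for outcomes well away from 50%.

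It would go too far to say that the odds ratios and intervals will be wrong. Near 50% prevalence the bias is moderate and coverage close to nominal. The sizes rest on the assumed covariate mix, a true odds ratio of 2, 20% attrition and illustrative outcome rates. Only secondary outcomes are involved; the primary CES-D analysis is not affected.

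**What to change.** In Outcome Evaluation, Data Analyses, state which approach the secondary outcomes inherit: the ANCOVA with baseline score, or the regression on dose and confounders. For binary outcomes, then choose one of two routes:
- keep the full list and fit it by Firth-penalised logistic regression; or
- limit each model to the baseline value of the outcome, dose and a short confounder set named in advance, sized to the expected number in the rarer outcome category.

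The sample-size section needs no change for this point, since it already ties its allowance to the CES-D regression. The cost is wording only, with no change to recruitment or data collection. The first route may need an add-on to the named software (SPSS 19.0); the second gives up some adjustment for confounding.

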### Study Design

This is a prospective one-group pre-test post-test study that aims to recruit 250 older home care clients with depressive symptoms who are using PSS. Assessments will be made at baseline (pre-test) and after the intervention, 6 and 12 months later (post-test). Descriptive and qualitative data will be collected to examine the feasibility and acceptability of the intervention and identify barriers and facilitators to implementation.

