Persistent Sleep Difficulties	Assess for change in sleep patterns; Educate client about sleep hygiene techniques, and non-pharmacological approaches to improve sleep; Refer client to physician for further assessment if sleep is identified as a major issue	[17]

Nutritional risk identified by Screen II Score: < 50/64 [137]	Nutrition education; Refer to Registered Dietitian Assess need for alternative feeding methods and/or supplements; Review medications and potential for food/drug interactions	[17]

ADLs indicates activities of daily living; Screen II, Seniors in the Community: Risk Evaluation for Eating and Nutrition, version II; OT, occupational therapist; PT, physiotherapist; CNIB, Canadian National Institute for the Blind; LTC, long-term care

• Redesigning the service delivery model to support the delivery of the nurse-led intervention, which involved: a) identifying a designated team of RNs and PSWs from two existing home care provider agencies to provide the nurse-led intervention, b) developing a detailed intervention protocol, c) establishing the referral process and guidelines for communication among providers and across agencies, d) developing home care provider and client materials to support the delivery of the intervention, and e) developing role-appropriate training manuals for the RNs and PSWs to standardize the intervention.

A four-pronged approach is used to implement the nurse-led intervention. First, the investigators held separate *educational workshops *for the RNs and PSWs. Each three day workshop was supported with role-appropriate standardized training manuals and a modified version of Nezu et al.'s [84] manual for PST. The workshops focused on the scope of the issue and effective evidence-based strategies for depression prevention, detection and management among older adults. The workshops were interactive, drew on participants 'experiences, and included demonstration of skills and opportunities for practice through role plays. These workshops were supplemented by a standardized eight-hour training workshop for the PSWs in the delivery of the HSEP.

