### Intervention

The nurse-led intervention consists of standard home care services plus home visitation by a designated team of RNs and a PSWs a minimum of once per month over a 6-month period. Standard home care services include routine follow-up by the CCAC case manager whose focus is on assessing the client's eligibility for in-home health services, arranging and coordinating professional (e.g., nursing, occupational therapy, physiotherapy, social work, speech-language pathology, and dietitian) and non-professional PSS, providing information and referral to community agencies, and monitoring and evaluating the plan of care on an ongoing basis through in-home assessments. The CCAC care coordinator determines eligibility and priority level for home care services and the amount and type of home care services required, based on set criteria [21].

The designated RN and PSW team provides a comprehensive, collaborative and evidence-based approach to the prevention, recognition and management of depression through regular home visits, standardized screening protocols, modification of risk factors for depression, depression education, support of antidepressant medication management, referral and linkage to health and social services, delivery of PST and social and behavioural activation, monthly case conferencing, and the development of a single, evidence-based depression management plan. The intervention, which is individualized to the client's needs, is coordinated by the RN. The RN provides leadership and coordinates communication between the client and their family caregiver, the PSW, the CCAC CM, the client's primary care physician (PCP), and other IP providers. The aim of the designated team of RNs and PSWs is to recognize, manage, and reduce the severity of depressive symptoms to enhance health-related quality of life (HRQOL) and reduce on-demand use of expensive health services. The frequency and timing of the home visits and case conferences is based on individual client needs and the results of the ongoing assessment of the client's progress toward the goals.

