We will also perform the following sensitivity analyses which will involve: a) use of multiple imputation to handle missing data, b) analysis of all outcomes analysed simultaneously using multivariate analysis of covariance (MANCOVA) to account for correlation among them, c) longitudinal analysis of data using generalized estimating equations (GEE) to account for the serial correlation of all outcomes at baseline, 6 and 12 months within a subject, and d) clustering among individuals who live together. The GEE is a technique that specifies the correlation structure between participants [111]. This approach produces unbiased estimates under the assumption that missing observations will be missing at random. An amended approach of weighted GEE will be employed if missingness is found not to be at random [111]. We will assume an autoregressive AR(1) correlation structure for the GEE analysis, which assumes that serial responses measured closer to each other are more correlated than those that are far apart.

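### The primary analysis has no term for the nurse or agency delivering the intervention, and clustering is considered only for co-residents; standard errors will be understated if outcomes correlate within nurse

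*Protocol article*

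**What the plan says.** The study has one group: "This is a prospective one-group pre-test post-test study that aims to recruit 250 older home care clients". Under Participants and Setting, everyone who consents and completes the baseline questionnaires goes on to the intervention. Development of the Intervention and Training describes the delivery model as "identifying a designated team of RNs and PSWs from two existing home care provider agencies to provide the nurse-led intervention". The Intervention section sets home visits by that team at monthly intervals or more often for six months, and adds: "The intervention, which is individualized to the client's needs, is coordinated by the RN". The RN also delivers the problem-solving therapy and develops the care plan.

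On analysis, Outcome Evaluation – Data Analyses names ANCOVA with the baseline score as covariate for the primary outcome, then regressions of change on dose and risk factors. No provider or agency term appears. The sensitivity analyses include a GEE for repeated measures within a participant and, as the last item, "clustering among individuals who live together". That is the only between-participant clustering mentioned. The sample size section contains no design effect.

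**The concern.** The plan recognises that participants may not be independent, but places the dependence in the household. The level built into the design is the provider: one RN presumably treats many participants, with repeated contact and a skill-dependent therapy. Co-resident pairs are likely to be few by comparison.

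In a one-group study, variation between RNs goes directly into the variance of the mean change; no second arm served by the same RNs exists for it to cancel against. An ANCOVA that treats participants as independent leaves that component out. This matters because the Discussion wants a model that works for varied providers and settings and expects the findings to apply elsewhere, so the conclusion is meant to reach beyond the RNs who took part.

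The dose and fidelity analyses are exposed too. Some fidelity items in Table 3 (training, monthly meetings with investigators) describe the provider rather than the client. Clustering inflates the standard error most for predictors that vary mainly between providers.

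**Working it through.** **Inputs from the article.** Target difference: "clinically important difference of 3.5 points in mean change from baseline to 6 months". SD: "Using a standard deviation of 9.0 as a conservative estimate and a difference of -3.5 points". Error rates: "two-tailed alpha = 0.05; beta = 0.20". Planned recruitment is 250 with 20% attrition allowed for, so 250 × 0.80 = 200 completers.

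**The plan's own figure.** The article states "a base sample size of 105 was estimated to be sufficient to address this primary outcome". The two-independent-means formula gives 2 × [(1.96 + 0.84) × 9.0 / 3.5]² ≈ 104 per group, or 105 with the t distribution, so 105 reproduces in that form. A one-sample test with an SD of change of 9.0 would need 52 (normal) or 54 (t). Equivalently, 105 fits a one-sample test if the SD of change is 9.0 × √2 = 12.73. The article does not say which SD is meant, so both are used below. Neither version includes clustering.

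**Assumptions not in the article.** k = 20, 10 or 6 RNs; equal caseloads m = 200/k; each client under one RN; ICC of the CES-D change 0.01 to 0.05.

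**Formulas.** Design effect DE = 1 + (m − 1) × ICC. True SE / naive SE = √DE. Actual two-sided level = 2 × [1 − Φ(1.96/√DE)].

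| RNs | m | ICC | DE | True SE / naive SE | Actual level |
|---|---|---|---|---|---|
| 20 | 10 | 0.01 | 1.09 | 1.04 | 6% |
| 20 | 10 | 0.05 | 1.45 | 1.20 | 10% |
| 10 | 20 | 0.01 | 1.19 | 1.09 | 7% |
| 10 | 20 | 0.05 | 1.95 | 1.40 | 16% |
| 6 | 33.3 | 0.01 | 1.32 | 1.15 | 9% |
| 6 | 33.3 | 0.05 | 2.62 | 1.62 | 23% |

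The true SE is thus 4–20%, 9–40% and 15–62% larger than the naive one for 20, 10 and 6 RNs. Seen from the other side, with 10 RNs the naive SE is 8–28% too small (1 − 1/1.09 and 1 − 1/1.40). At ICC 0, DE = 1.

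**Effect on the primary result.** With an SD of change of 9.0 the naive SE is 9.0/√200 = 0.64 and the 95% half-width 1.25 points. With 10 RNs and ICC 0.05 the SE is 0.89, the half-width 1.74 (2.01 on 9 degrees of freedom), and the effective sample size 200/1.95 = 103.

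Power for 3.5 points, normal reference, with a t reference on k − 1 degrees of freedom in brackets:

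| RNs | ICC | SD of change 9.0 | SD of change 12.73 |
|---|---|---|---|
| 20 | 0.01 | >99% (>99%) | 96% (94%) |
| 20 | 0.05 | >99% (99%) | 90% (86%) |
| 10 | 0.01 | >99% (99%) | 95% (89%) |
| 10 | 0.05 | 98% (94%) | 80% (70%) |
| 6 | 0.01 | >99% (96%) | 92% (77%) |
| 6 | 0.05 | 93% (77%) | 67% (49%) |

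With the SD of change at 9.0, power falls below 80% only with 6 RNs, ICC 0.05 and the t reference. With 12.73 it falls clearly short with 6 RNs and ICC 0.05 and, under the t reference, also with 10 RNs and ICC 0.05 and with 6 RNs and ICC 0.01.

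**The case against.** The strongest reply is that this is a condensed article, and random-effects structure is often left to an analysis plan. That would settle it if the article were silent. It is not: it lists clustering, locates it in the household, and specifies a primary model without a provider. Following the text as written gives the naive SE.

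Second, a reader might infer that the team is small and that the standard error is definitely too small. The documents support neither. They give no number of RNs or support workers, no caseload and no ICC. The understatement needs a positive ICC and a conclusion that treats these providers as a sample of a wider group. Nor does the article say that the RN alone fixes visit frequency (it ties this to client need and ongoing assessment), that RN identity is kept on visit records, or that each client has a single RN. If clients are shared between RNs, the simple design-effect formula does not apply as it stands. These limits stand, and they make the point conditional.

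Third, provider variation is partly addressed. Workshops, manuals, monthly outreach and monthly audit standardise delivery, and the Discussion plans to relate change to dose and fidelity. This may lower the ICC but does not put residual provider variance into the SE.

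Fourth, the primary conclusion is fairly robust: recruitment well above 105 leaves room, and the absence of a comparison group, which the authors acknowledge, is the larger threat to it. That stands too, and limits the severity.

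**Conclusion.** The point holds in conditional form. The primary analysis has no RN or agency term, and the household allowance, itself only a sensitivity analysis, does not stand in for one. Under any positive within-RN correlation, the reported intervals are too narrow and the p-values too small for the wider claim the article intends. The size cannot be fixed from the article: across the assumed range it runs from negligible (20 RNs, ICC 0.01) to a true level more than four times nominal (6 RNs, ICC 0.05). It would be wrong to infer that the trial loses its ability to detect 3.5 points; in most of the scenarios examined it does not. The main damage is to the precision claimed for the primary change, to the secondary outcomes, and to the dose analyses.

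**What to change.** Record the main RN for each participant. Analyse the CES-D change with an RN random intercept, or with standard errors clustered on RN, adding agency as a fixed effect (two agencies are too few for a random one) and a small-sample correction. Report the ICC. Treat the secondary and dose analyses the same way, and keep household clustering as secondary. If the existing GEE is re-clustered on RN, its AR(1) working correlation must be respecified, since it is defined for serial measurements within a participant.

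If there are very few RNs, or clients are shared between them, report the RN-level analysis as a sensitivity analysis beside the ANCOVA and limit the conclusion to the participating providers.

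The cost is one recorded variable and a somewhat larger model, with no extra visits. The price is a somewhat wider confidence interval and an ICC that will be imprecise.

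### The GEE sensitivity analysis rests on two missing-data rules that are each one step off: unweighted GEE is credited with validity under missing at random, and weighted GEE is reserved for data not missing at random

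*Protocol article*

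**What the plan says.** In the protocol article, Outcome Evaluation, Data Analyses, the primary test is an analysis of covariance on the change in CES-D from baseline to 6 months. The sensitivity analyses follow. One is "use of multiple imputation to handle missing data". Another is "longitudinal analysis of data using generalized estimating equations (GEE) to account for the serial correlation of all outcomes at baseline, 6 and 12 months". Three sentences govern the GEE analysis:

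- On validity: "This approach produces unbiased estimates under the assumption that missing observations will be missing at random".
- On the fallback: "An amended approach of weighted GEE will be employed if missingness is found not to be at random".
- On the working correlation: "We will assume an autoregressive AR(1) correlation structure for the GEE analysis".

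The GEE analysis therefore covers all outcomes, including the binary ones (prevalence of depressive symptoms and of anxiety), and all three visits.

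**The concern.** The three standard categories are missing completely at random (MCAR), missing at random given observed data (MAR) and missing not at random (MNAR). The article attaches the wrong category to each method.

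1. Unweighted GEE is consistent in general under MCAR, or when missingness depends only on covariates in the model. If dropout depends on earlier observed outcomes, which is MAR, consistency is not guaranteed.
2. Weighting each observation by the inverse of its estimated probability of being observed, given observed history, is what makes GEE valid under MAR. It does not deal with MNAR, because the weights cannot depend on values that were never seen.
3. For the same reason, no examination of observed data can establish MNAR, so the literal trigger for weighted GEE cannot be applied.

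An analyst following the text would use unweighted GEE where weighting is needed, and would present weighted GEE as a correction where it is none. The study has no comparison group, a limitation that its Discussion acknowledges. Bias from loss to follow-up therefore enters the before-after change directly, with no control arm in which it might partly cancel. The 12-month visit matters most, because the article uses it to judge whether any change is maintained.

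**Working it through.** The article gives no figure for bias from missing data, so there is none to reproduce. The check is a simulation of the stated rules.

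**Inputs from the article** (Sample Size Calculation and Feasibility of Recruitment): target change -3.5 points; SD 9.0; 20% attrition allowance, so 250 × 0.80 = 200 participants with 6-month data. The earlier trial's 84% completion would give 250 × 0.84 = 210.

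**Assumptions not in the article:**
- Baseline CES-D mean 22, with a true change of -3.5 at both 6 and 12 months.
- SD 9.0 at each visit. At correlation 0.5 the SD of the change is then also 9 × √(2 × (1 - 0.5)) = 9.0.
- Correlation 0.3, 0.5 or 0.7, with a true structure of AR(1) or exchangeable.
- 20% lost by 6 months and 15% of the remainder by 12 months, leaving 0.80 × 0.85 = 68%.
- Log-odds of dropout rising by 0.10 per CES-D point, an odds ratio of exp(0.10 × 9) = 2.46 per SD. Dropout depends on the last observed score (MAR) or on the current, unobserved score (MNAR).
- 400,000 simulated participants, so the standard error of a visit mean is about 9/√400,000 = 0.014.

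Bias is the estimated mean change minus -3.5. A negative value exaggerates improvement. Ranges run over the three correlations, and over both true structures unless one is named.

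| Analysis | Dropout | Bias, 6 months | Bias, 12 months |
|---|---|---|---|
| Unweighted GEE, independence | MAR | -0.41 to -0.99 | -0.45 to -1.70 |
| Unweighted GEE, AR(1), truth AR(1) | MAR | -0.01 to -0.03 | -0.04 to -0.08 |
| Unweighted GEE, AR(1), truth exchangeable | MAR | -0.03 to -0.06 | -0.31 to -0.42 |
| GEE weighted on observed history | MAR | -0.01 to +0.03 | 0.00 to +0.03 |
| Unweighted GEE, AR(1) | MNAR | -0.75 to -1.32 | -1.13 to -1.43 |
| GEE weighted on observed history | MNAR | -0.75 to -1.32 | -0.81 to -1.39 |

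**First rule.** The independence row shows that the general statement fails. With the planned AR(1) and a continuous outcome, the working correlation supplies most of the correction, so little bias remains at 6 months. The 12-month result depends on AR(1) being right. With 0.5 between adjacent visits, AR(1) implies 0.5² = 0.25 between baseline and 12 months, whereas an exchangeable truth has 0.5. That mismatch costs up to 0.42 points, or 0.42/3.5 = 12% of the target change. Binary outcomes were not simulated. For them even a correct working correlation carries no general guarantee under MAR.

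**Second rule.** Weighting removes the bias under MAR. Under MNAR it leaves 0.75/3.5 = 21% to 1.39/3.5 = 40% of the target change. At 6 months the range is the same as for unweighted AR(1) GEE, so the fallback gains nothing in the situation for which it is reserved.

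**The case against.** The strongest defence is that this is a slip of one term. If at random is read as completely at random in both sentences, the scheme is sound in outline: GEE under MCAR, and weighted GEE once missingness is seen to depend on observed data. That trigger can be examined. The reading is plausible and may be what the authors meant, but the text does not say it and an analyst has to follow the text. Even on this reading nothing in the plan addresses MNAR, since multiple imputation in its usual form also assumes MAR.

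A second defence is that the effect is limited. GEE is a sensitivity analysis, the primary is an analysis of covariance, and the planned AR(1) GEE is nearly unbiased at 6 months under MAR. This stands, and it lowers the weight of the point.

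Two stronger inferences are tempting, and the documents support neither.

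- A reader might infer that the primary is a complete-case analysis and so contradicts the claim to work "on an intention-to-treat basis". The article does not say how a missing 6-month CES-D enters the primary. That detail may sit in an analysis plan that is not shown, and placing multiple imputation among the sensitivity analyses is not an error.
- A reader might infer that completers necessarily overstate improvement. The direction depends on the mechanism. In the same simulation the completers' raw 6-month change was biased by +0.45 to +1.02 under MAR, which understates improvement, and by -0.42 to -1.01 under MNAR. An analysis of covariance in completers, evaluated at the full-sample baseline mean, was within 0.02 of zero when loss depended on baseline score, but off by -0.75 to -1.32 under MNAR.

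The article also plans proxy respondents and retention measures, which may keep loss below the 20% allowance.

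**Conclusion.** The point holds for the two GEE rules. The validity claim for unweighted GEE is too strong, and the trigger for weighted GEE can be neither applied nor effective as written.

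For the planned AR(1) GEE under MAR the practical exposure is small at 6 months. It is about 0.3 to 0.4 points at 12 months if AR(1) is misspecified, and it is unquantified for the binary outcomes. The larger risk is false assurance: under MNAR, weighted GEE would be reported as corrected while still off by roughly 0.75 to 1.4 points.

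These sizes rest on the assumed dropout rates, dropout slope and correlations. The logical errors do not. The point should be corrected before analysis, but it concerns a sensitivity analysis and does not by itself undermine the primary result.

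**What to change.** 1. State that unweighted GEE assumes data missing completely at random, or missingness depending only on covariates in the model.
2. Name one MAR analysis and run it regardless of what the data show: weighted GEE with weights from observed history, GEE after multiple imputation, or a likelihood-based mixed model. If unweighted GEE is kept, do not let the 12-month conclusion rest on AR(1) alone.
3. Delete the rule that switches to weighted GEE when missingness is found not to be at random. Put in its place a delta-adjusted (tipping-point) analysis of the 6-month CES-D change, with the range of shifts for unobserved scores set in advance.
4. Handle deaths separately, since a CES-D score after death is undefined.

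The cost is a few sentences and modest programming. No new data, visits or participants are needed.
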